### 9. Blinding and contamination

As with many obstetric interventions blinding is virtually impossible. The main outcomes of this study are self-reported and the women are clearly not blinded to their treatment allocation. However, we will institute a number of measures aimed at keeping antenatal staff blind to the treatment allocation and preventing contamination of the control group:

• Women will review the decision aid with the research nurse and complete the first questionnaire (primary outcome measures) prior to their next antenatal consultation

• Usual antenatal care providers will be blinded to the exact content and format of the decision aid

• Regular in-service (educational training) for the antenatal care providers to explain the trial protocol and to make clear the potential effect of unmasking or contamination.

• Monitoring decision aid distribution and keeping them locked up and only accessible by the research nurse

• Asking participants not to reveal their treatment allocation, or share their decision aid material with antenatal staff or other women. If participants do not want to keep their decision aid they will be asked to return it.

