### 10 outcome measures

#### Primary outcomes

The primary outcomes of this study will be:

*Decisional conflict *(uncertainty about which preference to choose) will be assessed by the Decisional Conflict Scale which has established reliability, good psychometric properties and is short (16 items) [31]. It has been used to evaluate a range of decision aids [1].

*Measures of knowledge and realistic expectations *about labour analgesia options and the benefits and risks of these options will be specific to this project. Thus we will need to develop, and test these measures as part of the project.

*Anxiety *will be measured by the state component of the short Spielberger anxiety scale which has been extensively used and validated [30,32]. We do not anticipate the decision aid will increase women's anxiety but it is important to document any changes in anxiety associated with the decision aid.

*Satisfaction *with analgesia decisions will be assessed using the Satisfaction with Decision Scale – a very brief six item scale with high reliability was developed specifically to assess satisfaction with health care decisions [33].

Satisfaction with the decision and anxiety will be measured again at 12–16 weeks postpartum. This interval was chosen to avoid the potential bias arising from questioning women still in the hospital who may feel a disloyalty to their caregivers by a critical appraisal and whose opinions have been shown to be more positive and short-lived than those obtained further out from the birth itself [34]. At that time we will also ask about exposure to the decision aid (to assess contamination), support during labour and use of pain relief methods prior to hospital admission. These issues will be further explored in the sample selected for in-depth interview.

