### 11 statistical issues

#### Sample size

The planned sample size is 600 women, with approximately 200 women to be recruited to each arm of the trial. Based on data for 2001 from the tertiary obstetric hospital where the study will be conducted, about 1500 primiparous women give birth to singleton infants after 36 weeks gestation and 92% use some form of analgesia. We anticipate that at least 50% of women will be both eligible and willing to participate.

The sample size calculations for the trial (significance 0.05, power 0.8) are based on the mean difference in the decisional conflict scale between any two arms of the trial. The effect of decision aids on this scale is documented and effect size data are available [1]. Meta-analysis of four randomised controlled trials comparing a decision aid to a pamphlet and that report a mean difference in decisional conflict gives a pooled mean difference of -4.35, 95%CI -6.8, -1.9 (on a scale ranging from 0 lowest to 100 highest decisional conflict; median standard deviation 13.0) [35-38]. Assuming a mean difference of -4.35 and standard deviation 13.0, we will need about 141 women in each arm of the trial to demonstrate a difference in decisional conflict.

Approximately 20% of primiparous women have a caesarean section (6% before labour and 14% after labour has commenced) [12]. Some of these women will lose their options for analgesia, although some may have extensive use of analgesic agents prior to caesarean section (CS). We plan to conduct an a priori sub-group analysis that excludes women who lose their options for analgesia (defined as a CS planned after randomisation, an emergency CS within 1 hour of arriving in labour or those who receive a therapeutic epidural) as these women may have different satisfaction, anxiety and decisional conflict outcomes. We will inflate the sample size estimate by 20% (from 141 to 169) to ensure sufficient power in the sub-group analyses. A further inflation of 15% for loss to follow-up, gives the final sample size of at least 195 women in each arm of the trial.

If there are no significant differences in outcome for the two decision aid groups (with or without the audio-component), the decision aid groups will be pooled giving two women with the intervention for each woman in the pamphlet group thereby increasing the power to detect differences between the decision aid and the pamphlet.

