#### Data analysis

Analyses will be by intention to treat, including withdrawals and losses to follow-up firstly of all women randomised and then excluding women who lose their options for analgesia. Study groups will be compared in terms of baseline characteristics. As this is a randomised trial, we would anticipate minimal differences in baseline characteristics. If however, important differences are found, these potential confounders will be adjusted for in the analysis of outcomes. For the primary outcomes, the mean score for each measure for each group will be compared using t-tests. If adjustment for confounders is needed a multiple linear regression model will be used. The secondary outcomes will be compared using chi-squared tests of significance for categorical data and t-tests for continuous data. If adjustment for confounding is necessary logistic regression and multiple linear regression will be used respectively.

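### The repeat analysis that drops women for events after randomisation is not intention to treat, has little basis for decisional conflict and knowledge, and selects on some secondary outcomes

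*Protocol article*

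**What the plan says.** The Sample size section announces "an a priori sub-group analysis that excludes women who lose their options for analgesia". Three events define the group: a caesarean that comes to be planned once the woman has been randomised, an emergency caesarean in the first hour after she arrives in labour, and a therapeutic epidural. The reason given is that these women may differ in satisfaction, anxiety and decisional conflict.

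The Data analysis section calls the analyses intention to treat and carries them out "firstly of all women randomised and then excluding women who lose their options for analgesia". It exempts no outcome from the second step.

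On timing, section 9 has women "complete the first questionnaire (primary outcome measures) prior to their next antenatal consultation". Section 6 puts antenatal visits at weekly intervals, and section 5 admits women from 36 weeks. The Primary outcomes section adds one later assessment: "Satisfaction with the decision and anxiety will be measured again at 12–16 weeks postpartum". No repeat of decisional conflict or knowledge is described.

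The exclusion analysis also enters the sample size. From a base of 141 per arm, the plan adds 20% for this analysis, giving 169. Then "A further inflation of 15% for loss to follow-up, gives the final sample size of at least 195 women in each arm".

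**The concern.** There are three linked problems.

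- **Label.** An analysis that removes randomised women because of something that happened after randomisation does not preserve the randomised groups. Calling it intention to treat gives it a standing it does not have.
- **Reason.** The plan expects the excluded women to differ in decisional conflict, the outcome that sizes the trial. That score is recorded before labour, so what happens in labour cannot alter it. For this outcome, and for knowledge, removing the women mostly discards usable scores.
- **Selection on outcomes.** Mode of delivery and pain relief used are secondary outcomes, and section 2 hypothesises that the decision aid does not influence them. The trial tests that hypothesis and cannot assume it when choosing whom to analyse. Taken literally, the Data analysis section compares mode of delivery after removing women according to mode of delivery.

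If the two analyses disagreed, a reader of the results could give the second one weight it does not deserve.

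**Working it through.** **Timing by outcome**

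| Outcome | When recorded | Can an event in labour affect it? |
|---|---|---|
| Decisional conflict, knowledge | First questionnaire, antenatal | No |
| Satisfaction, anxiety (first measurement) | First questionnaire, antenatal | No |
| Satisfaction, anxiety (repeat) | 12–16 weeks postpartum | Yes |
| Analgesia used, mode of delivery | At birth | The exclusion events are part of these outcomes |

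The stated reason therefore fits only the third row, apart from women whose options were lost before the first questionnaire.

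**The plan's sample size**

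Inputs from the Sample size section: "significance 0.05, power 0.8", difference 4.35, SD 13.0. Sidedness is not stated; two-sided reproduces the plan's figure.

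- Base: n = 2 × 13² × (1.960 + 0.842)² / 4.35² = 140.2, rounded up to 141 per arm. This agrees with the plan.
- Exclusion analysis: 141 × 1.20 = 169.2, given as 169.
- Loss: 169 × 1.15 = 194.35, given as 195.

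The chain reproduces. However, multiplying by 1.20 offsets an exclusion of only 1 − 1/1.20 = 16.7%, and multiplying by 1.15 offsets a loss of only 1 − 1/1.15 = 13.0%. Offsetting 20% and 15% in full needs 141 / (0.80 × 0.85) = 207.4, or 208 per arm. With the 15% loss alone, 141 / 0.85 = 165.9, or 166 per arm.

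**Power for decisional conflict, any two arms**

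Power = Φ(4.35 / (13 × √(2/n)) − 1.960), with n = N × 0.85 × (1 − share excluded).

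| Share excluded | N = 195: n, power | N = 200: n, power |
|---|---|---|
| 0% (all randomised) | 165.8, 86.1% | 170.0, 87.0% |
| 6% (assumed) | 155.8, 84.0% | 159.8, 84.9% |
| 10% (assumed) | 149.2, 82.4% | 153.0, 83.3% |
| 20% (caesarean rate in the plan) | 132.6, 77.8% | 136.0, 78.8% |

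The t distribution gives slightly lower values: 86.8% and 78.5% at 170 and 136 per arm, and about 77.5% at 195 per arm with 20% excluded. The 15% loss matters too: with no loss and 20% excluded, N = 195 leaves 156 per arm and 84.0% power.

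**Possible selection bias (assumed figures)**

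Suppose there is no true effect, excluded women score D points differently from retained women, and exclusion rates differ by x between arms. The spurious difference is then x × D. With x from 5 to 14 percentage points and D from 5 to 13 points, it runs from 0.05 × 5 = 0.25 to 0.14 × 13 = 1.82 points, or 6% to 42% of 4.35. It is zero if the arms lose the same proportion and the same kind of women. The protocol gives neither x nor D.

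**The case against.** The strongest reply is that the main analysis is untouched. All randomised women are analysed first, the exclusion step is called a sub-group analysis and is fixed in advance, and the full result always stands beside it. That is correct. A reader might infer that the trial discards primary data or that its main comparison is broken; the document does not support either.

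A second reply is that the reason is not empty for decisional conflict. A caesarean could be planned between randomisation and the first questionnaire, and a woman who has just lost her choice might well score differently. Therapeutic epidural is not defined, and section 5 already excludes women with a planned epidural, so one decided antenatally after randomisation is conceivable. This stands in part: it limits the criticism to losses of option that come after the questionnaire. It does not rescue the emergency caesarean criterion, and selection after randomisation remains.

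A third reply concerns size. The protocol does not say how many women meet the definition. The 20% is the whole caesarean rate, only some of those women qualify, and therapeutic epidurals add an unknown number. This stands, so a fall below 80% is conditional. It also depends on inflating by multiplication, which is a separate weakness.

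Finally, the reach to knowledge, utilisation and perinatal outcomes comes from the general wording of the Data analysis section. The reason in the Sample size section names only satisfaction, anxiety and decisional conflict. That is fair, and it is why the scope should be written down.

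**Conclusion.** The point holds as a correction to the scope, label and power basis of the second analysis. It is not intention to treat. Its reason fails for decisional conflict wherever options are lost after the first questionnaire, and for mode of delivery and analgesia used it selects on the outcome. That decisional conflict and knowledge are measured only once is inferred from sections 9 and 10, which describe no repeat.

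All-randomised power is about 86–87% at 195–200 per arm, assuming a 4.35-point difference, SD 13 and 15% loss. In the exclusion set it is about 77–79% if 20% are excluded and about 82–85% at an assumed 6–10%.

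Three stronger readings are not supported:

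- **That the scores precede labour by weeks.** Entry is from 36 weeks with no stated upper limit, so the gap may be short, and some women may deliver before the questionnaire.
- **That the second analysis is known to be biased.** Bias requires the arms to differ in how many or which women are excluded, and the protocol gives no figure for either.
- **That dropping the exclusion raises the trial's power.** All-randomised power is the same whether or not the second analysis is kept.

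**What to change.** 1. State that all first-questionnaire outcomes (decisional conflict, knowledge, antenatal anxiety and antenatal satisfaction), and all utilisation and perinatal outcomes, are analysed in all randomised women only.
2. Keep the exclusion analysis for satisfaction and anxiety at 12–16 weeks postpartum. Label it supportive and not intention to treat, and present it beside the all-randomised result.
3. Report the number excluded, by arm.
4. Justify 195–200 per arm by the all-randomised power of about 86–87%, in place of the 20% inflation.

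This is a change of wording. No data collection or recruitment target changes. The cost is that one supportive analysis is narrowed: the plan would no longer look separately at antenatal scores in women whose options were lost before the questionnaire.

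### The sample size is inflated by multiplying by 1.20 and 1.15 rather than dividing by 0.80 and 0.85, so the 20% allowance, if fully used, leaves the two-arm sub-group comparison slightly below 80% power

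*Protocol article*

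**What the plan says.** All of this is in the protocol article, section 11, Sample size.

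- Design values: "The sample size calculations for the trial (significance 0.05, power 0.8) are based on the mean difference in the decisional conflict scale", for the comparison of any two arms.
- Base size: "Assuming a mean difference of -4.35 and standard deviation 13.0, we will need about 141 women in each arm of the trial".
- Reason for the first allowance: "Approximately 20% of primiparous women have a caesarean section (6% before labour and 14% after labour has commenced"). The text adds: "Some of these women will lose their options for analgesia, although some may have extensive use of analgesic agents prior to caesarean section".
- The a priori sub-group leaves out women whose caesarean was planned after randomisation, women with an emergency caesarean within an hour of arriving in labour, and women given a therapeutic epidural. No expected proportion is given for any of these.
- First inflation: "We will inflate the sample size estimate by 20% (from 141 to 169) to ensure sufficient power in the sub-group analyses".
- Second inflation, a further 15% for loss to follow-up, which "gives the final sample size of at least 195 women in each arm of the trial".
- Recruitment target: 600 women, with "approximately 200 women to be recruited to each arm of the trial".

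The Data analysis section makes the sub-group analysis the second of two planned analyses, after the analysis of all women randomised.

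**The concern.** An allowance for exclusions or losses is meant to leave the required number after those women are gone. If a fraction d is removed from N, then N(1 − d) remain, so N must be n/(1 − d). Multiplying n by (1 + d) always falls short, because (1 + d)(1 − d) = 1 − d², which is below 1. The plan makes this slip twice in succession, and the shortfalls compound.

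At stake is the assurance attached to the first step, that the inflation secures enough power for the sub-group analysis. The only power figure in the section is 0.8. A reader would take it that the sub-group comparison keeps 80% power once the two allowances are used up, and on the plan's own percentages it does not quite do so.

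**Working it through.** **Inputs** (all from the Sample size section): mean difference 4.35; SD 13.0; significance 0.05; power 0.80; two arms compared 1:1; allowances of 20% and 15%; minimum 195 and planned 200 per arm. Sidedness is not stated. A two-sided test reproduces 141, while a one-sided test gives 111, so two-sided is used. Exclusion and loss are assumed independent and equal across arms.

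**1. Reproduce the base size.** n = 2 × (1.960 + 0.842)² × (13.0/4.35)² = 140.2, so 141 per arm. The t-test version gives 141.2. The plan's figure is confirmed.

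**2. Reproduce the inflation.** 141 × 1.20 = 169.2, printed as 169. Then 169 × 1.15 = 194.4, rounded up to 195. Division does not give the printed figures: 141/0.80 = 176.3, and 169/0.85 = 198.8. The plan therefore multiplied at both steps.

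**3. Size needed if 20% are excluded and 15% lost.** 141/(0.80 × 0.85) = 141/0.68 = 207.4, so 208 per arm (209 if each step is rounded up). That is 13 more than 195 and 8 more than 200.

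**4. What the stated sizes leave** (two-sided t-test, difference 4.35, SD 13.0):

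| Recruited per arm | Lost | Excluded | Evaluable per arm | Power | Difference detectable at 80% |
|---|---|---|---|---|---|
| 195 | 15% | 20% | 132.6 | 77.5% | 4.49 |
| 200 | 15% | 20% | 136.0 | 78.5% | 4.43 |
| 208 | 15% | 20% | 141.4 | 80.1% | 4.35 |
| 195 | 15% | 14% | 142.5 | 80.4% | – |
| 200 | 15% | 14% | 146.2 | 81.4% | – |
| 195 | 15% | none | 165.75 | 85.9% | – |
| 200 | 15% | none | 170.0 | 86.8% | – |

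The normal approximation gives values 0.2 to 0.3 points higher (77.8% and 78.8% in the first two rows).

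**5. Exclusion rate at which 141 women remain, with 15% lost.** At 195: 1 − 141/(195 × 0.85) = 14.9%. At 200: 1 − 141/(200 × 0.85) = 17.1%.

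**6. Loss rate at which 141 remain, with a full 20% excluded.** At 195: 1 − 141/(195 × 0.80) = 9.6%. At 200: 1 − 141/(200 × 0.80) = 11.9%.

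**The case against.** A reader might infer that the sub-group analysis definitely lacks 80% power, or that the trial as a whole is too small. The documents support neither.

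- **The exclusion rate is not stated to be 20%.** That figure is the overall caesarean rate, and the plan says only some of these women lose their options. Many caesareans after the onset of labour need not meet the one-hour rule, and caesareans already planned are excluded at entry (section 5). This stands, and it makes the shortfall conditional. In the other direction, women given a therapeutic epidural are also removed, at an unstated rate. The plan offers no lower figure than its 20% allowance.
- **The 15% loss may be high for this outcome.** Decisional conflict is collected in the first questionnaire, before the next antenatal consultation (sections 8 and 9), while only satisfaction and anxiety are named for repeat at 12–16 weeks postpartum (section 10). The plan does not say which follow-up the 15% describes. This also stands as a reason for wording the point conditionally.
- **No separate power is promised for the sub-group.** The text says sufficient power and gives no number. That is so, but 0.8 is the only standard the section sets.
- **195 is a minimum and about 200 are planned.** At 200 the shortfall is about 1.5 points.
- **Pooling the two decision aid arms raises power.** At a 2:1 ratio, with 20% excluded and 15% lost, it is about 88% to 89%. This does not rescue the statement: the calculation is for any two arms, pooling depends on finding no significant difference between the decision aid arms, and the comparison of audio with no audio can never gain from it.

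**Conclusion.** The inflation is computed wrongly, and the effect is small. If the whole 20% allowance is used and 15% are lost, power for the two-arm sub-group comparison is about 77.5% at 195 per arm and 78.5% at 200. That is 1.5 to 2.5 points below 80%, or a detectable difference of 4.49 or 4.43 points instead of 4.35. In that case the inflation does not secure 80%, and about 208 per arm would be needed. With 15% loss, 80% is kept if exclusions are no more than about 15% (195 per arm) or 17% (200 per arm). Whether they will be cannot be settled from the document.

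The analysis of all randomised women is not put at risk. The results rest on a two-sided test, the plan's SD of 13.0, and exclusion and loss that are independent and equal across arms.

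**What to change.** Keep 200 per arm. Show each inflation as division by one minus the proportion removed, and replace the assurance about sub-group power with figures, for example:

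> With 200 women per arm and 15% loss, power is about 87% for the analysis of all randomised women. If as many as 20% are also excluded (136 per arm), sub-group power is about 78%, or 80% for a difference of 4.4 points. It stays at 80% if no more than about 17% are excluded.

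The conditional wording matters, because it avoids writing a 20% exclusion rate into the plan as an expectation. The cost is a few restated sentences. Recruitment, design and analysis do not change.

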A number of draft decision aids (including workbook, audio transcript, and worksheet), were developed and each subjected to pilot testing and revision as we obtained feedback. The process of testing and revising started with the study project group. The next phase included a review by a group of national and international content experts, including decision aid experts, obstetricians, midwives, perinatal epidemiologists, parent educators and psychologists. Once we were convinced that the content was accurate the decision aid was pilot-tested amongst consumers. There were several rounds of consumer review and refinement.

Initially we aimed to compare the Decision Aid (workbook and audio-component) with usual care and counselling however preliminary work led us to alter our original study design. We could find no studies that compared Decision Aids with and without an audio-component. As the audio-component adds considerable complexity to the development and cost of the Decision Aid we decided to have two intervention arms: a Decision Aid with an audio-component and a Decision Aid without an audio-component. Further in pilot testing we found that women in the usual care arm were disappointed to not receive any information. Thus, to minimise refusals and losses to follow-up we decided to issue the women in the control group with a pamphlet called "Pain relief during childbirth – A guide for women" This pamphlet is published by the Royal Australian and New Zealand College of Obstetricians and Gynaecologists, is publicly available and includes information about methods of pain relief during labour [29]. These changes to the study protocol were approved by the institutional ethics committee prior to commencement of the trial.

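### A non-significant audio versus no-audio test decides whether the two decision-aid arms are pooled; the contrasts with the pamphlet should be fixed in advance

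*Protocol article*

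**What the plan says.** The last paragraph of section 11, Sample size, in the protocol article sets the rule: "If there are no significant differences in outcome for the two decision aid groups (with or without the audio-component"), then "the decision aid groups will be pooled giving two women with the intervention for each woman in the pamphlet group". The reason given is more power against the pamphlet. No equivalence margin is attached, and the text does not say that each aid will still be compared with the pamphlet after pooling.

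The same section bases the sample size on the "mean difference in the decisional conflict scale between any two arms of the trial", at significance 0.05 and power 0.8: "Assuming a mean difference of -4.35 and standard deviation 13.0, we will need about 141 women in each arm of the trial". The 4.35 comes from a "Meta-analysis of four randomised controlled trials comparing a decision aid to a pamphlet".

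The section on development of the decision aid gives the cost and complexity of the audio component as the reason for having two aid arms, and states: "We could find no studies that compared Decision Aids with and without an audio-component". The Data analysis section plans t-tests on group means and mentions no adjustment connected with the pooling step.

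**The concern.** The rule treats failure to find a difference between formats as licence to treat them as one. It also lets the trial's own outcome data choose which contrast with the pamphlet is the main result. Three things follow.

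- The deciding test has a planning difference borrowed from another comparison. Its 80% power holds only if adding audio to the workbook gains as much as a whole decision aid gains over a pamphlet. The documents offer no figure for the audio increment.
- When audio adds something smaller, an inconclusive audio result is likely. The arms are then merged, and the workbook-only format shares whatever the combined contrast shows.
- The value of the audio component is why there are two aid arms, yet an inconclusive answer to that question removes the separation between them.

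**Working it through.** **Inputs.** From section 11: difference 4.35, SD 13.0, significance 0.05 (taken as two-sided, which reproduces the stated size), power 0.8, about 200 women per arm, 15% loss to follow-up. Evaluable per arm: 200 × 0.85 = 170. Assumed here: audio increments of 2.175 (half of 4.35) and 3 points.

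**The plan's own figure.** n = 2 × (1.96 + 0.8416)² × 13² / 4.35² = 140.2 by the normal formula; the t-based value is 141.2. The stated 141 is reproduced. So are the inflations: 141 × 1.20 = 169, and 169 × 1.15 = 194.4, about 195.

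**Power of the deciding test (audio versus no audio).** The standard error at 170 per arm is 13 × √(2/170) = 1.41.

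| True audio increment | 141 per arm | 170 per arm | 200 per arm |
|---|---|---|---|
| 4.35 (planned difference) | 80% | 87% | 92% |
| 3 (assumed) | 49% | 56% | about 63% |
| 2.175 (assumed) | 29% | 34% | 39% |

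Detectable difference at 80% power: (1.96 + 0.8416) × 1.41 = 3.95, about 4.0 points. 95% CI half-width: 1.96 × 1.41 = 2.76, about 2.8 points.

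**Is the pooled test distorted by the preliminary test?** No. With equal arm sizes and SDs, Cov[A − W, (A + W)/2 − P] = Var(A)/2 − Var(W)/2 = 0, where A, W and P are the means of the audio, workbook-only and pamphlet arms. The two contrasts are independent, so the pooled test keeps 5.0% given that pooling occurred. Simulation with 3 million replicates agrees.

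**Overall error when no arm has any effect.** Assume that, if the deciding test is significant, each aid is tested against the pamphlet at an unadjusted 0.05. In that branch a false claim occurs about 37% of the time. Overall: 0.95 × 0.05 + 0.05 × 0.37 = 0.066, or 6.6%. Two unadjusted pairwise tests with no pooling rule would give 9.1%.

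**False credit to the workbook-only aid** (audio works, workbook alone has no effect, 170 per arm, simulated). A trial counts if the arms are pooled and the pooled test is significant, or if they are not pooled and the workbook-only test is itself significant (two-sided).

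| Audio effect | Arms pooled | Pooled test significant | Product | Total, with unpooled branch |
|---|---|---|---|---|
| 2.175 | 66% | 14.5% | 9.6% | 11.7% |
| 3 | 43% | 23% | 10.1% | 12.8% |
| 4.35 | 13% | 43% | 5.6% | 9.3% |

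A fixed test of workbook-only versus pamphlet gives 5% in every row.

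**Both formats work, unequally** (−4.35 with audio, −2.175 without). The arms are pooled in 66% of trials. The pooled estimate averages −(4.35 + 2.175)/2 = −3.26, which is 3.26/2.175 = 1.5 times the true workbook-only effect.

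**Contrasts fixed in advance, 170 per arm.** Combined aids (340) versus pamphlet (170): standard error 13 × √(1/340 + 1/170) = 1.22, giving 94% power for 4.35. If each aid is then tested at 0.05 only after a significant combined test:

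- error under no effect is 5.0%;
- power is about 86% per aid if both have the 4.35 effect;
- false credit to an inert workbook is about 2.5% (audio effect 3);
- combined power is 43% if the effects are −4.35 and 0, because the average is then 2.175.

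**The case against.** The strongest defence has four parts.

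- **Validity of the pooled test.** A reader might infer that the preliminary look invalidates the pooled p-value and interval. It does not, because the two contrasts are independent. The excess from 5.0% to 6.6% arises only in the unpooled branch and only if its pairwise tests are unadjusted, which a fuller analysis plan may settle. This stands.
- **Power.** A reader might call the deciding test underpowered outright. At the only difference the plan states, it has 80% power at 141 per arm and 87% at 170. Shortfalls appear only at increments assumed here. This stands, but the 4.35 is still borrowed from a different comparison, and high power at 4.35 does not turn a non-significant result into evidence of sameness.
- **Attribution.** The aim and hypotheses concern the decision aid without separating formats. Nothing says a pooled result will be credited to the workbook alone, and the Data analysis section can be read as keeping each group visible. So misattribution is a risk the rule creates, not an announced intention. Which of the several primary outcomes governs pooling may also be left to a fuller document, and is not pressed here.
- **Cost of always pooling.** Compulsory pooling with nothing else would be a poor remedy. If only the audio format works (−4.35 and 0), the combined test has 43% power, whereas the present rule makes some claim against the pamphlet in about 86% of trials. This stands, and it is why the separate comparisons must always be reported.

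**Conclusion.** The conditional pooling rule should be replaced. Its fault is that it reads non-significance as sameness and lets that reading choose the main contrast, for a pair of arms with no planning difference of its own. The size is moderate: an inert workbook-only aid would share a significant result in about 9–13% of trials instead of 5%. With effects of −4.35 and −2.175, the arms would be pooled in about two-thirds of trials and the combined estimate would overstate the workbook-only effect by half. Inflation of the false-positive rate is a minor part of the case.

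These figures assume SD 13, 170 evaluable women per arm, decisional conflict as the only outcome, unadjusted pairwise tests when the arms are not pooled, and audio increments that the documents do not supply. The documents do not support the stronger conclusion that the main test is invalid or that the trial is too small. This is a should-fix point.

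**What to change.** Delete the conditional sentence and fix the contrasts in advance, whatever the audio result. One suitable wording: *Both decision-aid arms combined will be compared with the pamphlet at the 0.05 level. If this is significant, each decision aid will be compared with the pamphlet at the 0.05 level. Each aid versus pamphlet, and audio versus no audio, will always be reported as estimates with 95% confidence intervals. A non-significant audio comparison will not be interpreted as equivalence.*

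In the sample-size section, state that −4.35 applies to decision aid versus pamphlet, and that the audio pair can detect about 4.0 points at 80% power with a confidence-interval half-width of about 2.8 points.

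The cost is a few sentences and no extra women. The downside to state openly is the loss of power of the combined contrast when only one format works (43% at effects −4.35 and 0). If the sponsor thinks that likely, two comparisons with the pamphlet at 0.025 each need 170 evaluable women per arm for 80% power, which also fits the planned 200. Either choice must be made before outcome data by arm are seen.
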